#### Quantitative Data Collection and Storage

Quantitative data will be collected at baseline, at 8-month follow-up, and via the Nishauri app data. At baseline, potential participants will be screened for eligibility. Eligible participants will provide written informed consent and locator information before undergoing a short baseline survey lasting approximately 40 minutes. The survey includes validated and pilot-tested modules on sociodemographics, technology acceptance, HIV-related stigma, health literacy, masculinity norms, the System Usability Scale, and intervention acceptability. The survey will be administered electronically using tablets with the REDCap (Research Electronic Data Capture) platform, hosted by the San Francisco Coordinating Center. Data will be collected by trained research assistants (RAs), who were locally recruited and had prior experience in health or social science research. RAs have backgrounds in public health or related disciplines; are fluent in English, Kiswahili, and Dholuo; and will receive study-specific training on the study protocol, ethical conduct of research, informed consent, and standardized data collection procedures prior to data collection. RAs will perform daily quality checks on all forms to identify and resolve errors prior to secure upload to REDCap servers. These servers are firewall-protected, regularly backed up, and housed in a secure environment.

Throughout implementation at each site, app-based metrics will be assessed to capture implementation outcomes related to acceptability and uptake of the Nishauri intervention. Facility-based data will be collected, including who gets the intervention, the date of training, and the date of app installation. App analytics will be used to capture patterns of engagement and uptake among participants. This includes the number of log-ins per user, frequency of use over time, cumulative duration of app sessions, and responsiveness to reminders and notifications (whether SMS or in-app prompts were opened or acted upon). Aggregate metrics such as average log-ins per month, median engagement time, and drop-off points will be analyzed to assess acceptability and sustained use across the study period.

All data will be transferred securely to the San Francisco Coordinating Center network via a secure File Transfer Protocol site under a formal data transfer agreement between the University of California, San Francisco, and the local research center. Data will be stored on encrypted, password-protected servers with limited access, using study ID numbers in place of participant names. Physical documents will be stored securely onsite, and all sensitive data will be separated from identifying information to ensure confidentiality.

#### Quantitative Data Analysis

Descriptive statistics will be used to summarize demographic variables, intervention adoption, and predictors of adoption (health literacy, technology acceptance, and masculinity). A participant will be considered to have adopted Nishauri if he has completed device installation and created or activated an account within 60 days of being trained or introduced to the app. Participants who occasionally attend multiple facilities will be documented, and their data will be analyzed based on their primary facility of care. This aligns with national HIV care guidelines, which encourage patients to register at a single facility for longitudinal HIV treatment and monitoring.

#### Power Calculation for the Pre- and Postassessment

With 347 participants, an anticipated 10% attrition rate (effective n≈312), and a primary binary uptake outcome, the study will have adequate power to examine associations between key predictors (health literacy, technology acceptance, and masculinity) and adoption of Nishauri. Assuming an uptake rate of ~70% (adopters: n≈243; nonadopters: n≈104) as seen in other studies [22,23], we will have >80% power (*α*=.05) to detect moderate associations corresponding to odds ratios of roughly 1.7‐2.0 or higher, depending on predictor prevalence. Sensitivity analyses showed that with effective sample sizes ranging from 280 to 330 participants, the study would retain ≥80% power to detect odds ratios between 1.7 and 2.0, depending on predictor prevalence.

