In parts of Homa Bay and other counties where Nishauri has been implemented on a pilot basis for over 6 months, its uptake and use remain low and highly variable across facilities, providers, and patient populations. This variability hints at challenges with its implementation and effectiveness among men, a population that faces unique sociocultural barriers to HIV care. Existing research often overlooks the role of gender norms and contextual factors in influencing men’s engagement with digital health interventions. Addressing this gap is essential for designing scalable, culturally relevant mHealth solutions that promote sustained engagement and improved clinical outcomes among men. This study will be guided by an integrated conceptual framework combining Connell’s theory of hegemonic masculinity [29] and the technology acceptance model (TAM) [30,31] to underpin the design and evaluation of Nishauri, predicting how individual factors (eg, perceived usefulness, usability, and masculinity norms) and system-level factors (eg, workflow integration and provider support) influence adoption, engagement, and sustainment of the intervention.

This study aims to assess the implementation and potential effects of the Nishauri mHealth intervention on HIV care and treatment outcomes among men aged 18‐55 years in Homa Bay County, Western Kenya. Specifically, it seeks to (1) analyze its potential effects on HIV care and treatment outcomes, (2) explore the role of masculine identity in modifying its acceptability and uptake, and (3) identify barriers and facilitators of its adoption, use, and sustainment.

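### The adoption power rests on an uptake of about 70% that is not reconciled with the low local pilot uptake the protocol reports, and its sensitivity analysis varies only sample size

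*Protocol article*

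**What the plan says.** The section on power for the pre- and postassessment starts from 347 men and "an anticipated 10% attrition rate (effective n≈312"). It continues: "Assuming an uptake rate of ~70" per cent, "as seen in other studies [22,23"], which it converts to about 243 adopters and 104 nonadopters. On that basis "we will have >80% power" at alpha 0.05 for "moderate associations corresponding to odds ratios of roughly" 1.7 to 2.0 or higher, depending on predictor prevalence. The predictors are health literacy, technology acceptance and masculinity.

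The robustness check covers one input: "Sensitivity analyses showed that with effective sample sizes ranging from 280 to 330 participants", the study would keep at least 80% power for odds ratios between 1.7 and 2.0. Uptake stays fixed.

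The Introduction reports that where Nishauri has been piloted for over 6 months, in parts of Homa Bay and other counties, "its uptake and use remain low and highly variable across facilities, providers, and patient populations". It reads this as a hint of implementation problems among men. It gives no percentage.

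**The concern.** For a binary outcome, power depends on the smaller of the two outcome groups. At 70% uptake that is the nonadopters. If uptake were well below 30%, it would be a smaller group of adopters. Uptake is therefore an input that can move the power a great deal, and it is the one the protocol's own text makes most doubtful. The four study facilities lie in the county where the pilot partly ran, and variation across facilities matters when there are only four.

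The analysis is not peripheral. Adoption is the primary implementation outcome, and the role of masculine identity in acceptability and uptake is the second objective. The section claims adequate power without a condition on uptake. A null result for masculinity, health literacy or technology acceptance could then be read as evidence of no association when the study may have had little chance of finding one.

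**Working it through.** **Inputs from the protocol.** Planned n 347; attrition 10%, effective n about 312; uptake about 70%; odds ratio (OR) 1.7 to 2.0; alpha 0.05; sensitivity range 280 to 330; 307 men reported as recruited (Results).

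**Assumptions.** The predictor is binary with 50% prevalence (the protocol speaks of predictor prevalence but gives no value). The test is two-sided, as the protocol states for the stepped-wedge analysis. Uptake values other than 70% are illustrative. Applying the 10% loss to the 307 recruited gives 307 × 0.9 = 276.

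**Method.** Let p0 and p1 be the adoption probabilities in the two predictor groups. Solve (p0 + p1)/2 = uptake and p1(1 − p0)/[p0(1 − p1)] = OR. The standard error of the log odds ratio is the square root of the sum of the reciprocals of the four expected cell counts. Power is Φ(ln OR/SE − 1.96).

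**Step 1: the plan's own figure.** Uptake 70%, OR 2.0, n = 312:

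- p0 = 0.628 and p1 = 0.772.
- With 156 men per group the cells are 98.0, 58.0, 120.4 and 35.6.
- SE = √(0.0102 + 0.0172 + 0.0083 + 0.0281) = 0.253.
- ln 2/SE = 0.693/0.253 = 2.74, so power is Φ(0.78) = 78%.

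A pooled two-proportion test gives 79%. For OR 1.7 the two methods give 56% and 57%.

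Other readings:

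- With all 347 men and no attrition, OR 2.0 reaches about 83% and OR 1.7 about 61%.
- A one-sided test at n = 312 gives 87% and 69%.
- At predictor prevalence 30%, power for OR 2.0 at n = 312 falls to 66-68%.

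The claim above 80% is therefore met or nearly met at OR 2.0 with a balanced predictor. It is not met at OR 1.7 under any binary-predictor reading tried.

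**Step 2: vary uptake.** OR 2.0, n = 312. At 20% uptake, p0 = 0.146, p1 = 0.254 and SE = 0.292, so power is Φ(2.37 − 1.96) = 66%. At 10%, p0 = 0.070, p1 = 0.130 and SE = 0.394, so power is Φ(1.76 − 1.96) = 42%.

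| Uptake | Power, n = 312 | OR detectable with 80% power, n = 312 | Power, n = 276 |
|---|---|---|---|
| 70% | 78% | 2.0 | 73% |
| 50% | 85% | 1.9 | 81% |
| 40% | 84% | 1.9 | 79% |
| 30% | 78% | 2.0 | 73% |
| 20% | 66% | 2.3 | 61% |
| 10% | 42% | 3.3 | 38% |

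The pooled test at n = 312 gives 67% at 20% uptake and 43% at 10%, so the pattern does not depend on the formula. With all 347 men the log-odds-ratio calculation gives 71% and 46%. At 10% uptake there are about 31 adopters (312 × 0.10).

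**Step 3: what the plan's sensitivity range shows.** At 70% uptake and OR 2.0, moving n from 280 to 330 moves power from about 74% to about 81%. Moving uptake from 30% to 10% at n = 312 moves it from 78% to 42%. The check varies the input that matters less.

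**The case against.** The strongest reply is that the two statements describe different groups. The pilot remark concerns uptake and continued use across mixed facilities, providers and patients. The power calculation concerns consenting smartphone or tablet owners aged 18 to 55, who are trained to install the app, have peer-educator follow-up, and count as adopters once they install and activate within 60 days. Low pilot uptake and 70% in this cohort can both be true. That stands. A reader might infer that the protocol contradicts itself or that 70% is wrong, but the documents do not show either. What remains is that the power section does not make this argument.

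A reader might also infer that local uptake is 10-20%, so true power is 42-66%. The protocol gives no pilot figure, so those values only illustrate a range.

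Nor does lower uptake always cost power. Between 30% and 70%, power is equal to or higher than at 70%. Uptake has to fall to less than half the assumed rate before there is harm.

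Finally, the predictors come from survey modules and their coding is not fixed. If they were analysed as continuous scores with the odds ratio per standard deviation, power at n = 312 and 10% uptake would be about 80% for OR 1.7 and 96% for OR 2.0. The protocol's reference to predictor prevalence favours the binary reading, but it would be too strong to say that the analysis cannot detect the stated associations. This is a reason to state the coding.

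**Conclusion.** The point holds as one of justification and sensitivity. The uptake input is taken from elsewhere, is not reconciled with the protocol's own account of the app in the same county, and is left out of the sensitivity analysis.

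For a balanced binary predictor, a two-sided 5% test and OR 2.0, power at n = 312 is about 78% at the assumed 70%. It holds or improves down to 30%, then falls to 66% at 20% and 42% at 10%. On the men recruited less 10%, it is 73%, 61% and 38% at 70%, 20% and 10%.

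It would be wrong to put the whole gap from 80% down to uptake. At the plan's own 70% and n = 312, power already sits just under 80% for OR 2.0 and at 56-57% for OR 1.7, so there is no margin to absorb low uptake. The size of the effect rests on assumed uptake values, predictor prevalence and binary coding. That uptake was not varied is plain from the text.

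**What to change.** In the section on power for the pre- and postassessment:

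1. Say why about 70% is expected in this cohort given the pilot experience in the Introduction, for example through device ownership, training and the 60-day definition.
2. Replace the statement of more than 80% power for odds ratios 1.7 to 2.0 with power and the detectable odds ratio over an uptake range labelled as an assumption, for example 10% to 70%, at the achieved sample size. At n = 312 the detectable odds ratio is about 2.0 at 30% or 70% uptake, 2.3 at 20% and 3.3 at 10%. At n = 276 it will be somewhat larger.
3. State the predictor coding and prevalence assumed.

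The cost is a short rewrite and one table. Design and sample size do not change. The stated power becomes less favourable, and readers gain a basis for interpreting a null predictor result once the observed uptake is known.

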**Results:**

This study received institutional review board approval in July 2025 and was registered on ClinicalTrials.gov in August 2025. Recruitment began in September 2025 and concluded in November 2025. A total of 307 men living with HIV were recruited across the 4 clinics for the pre- and postquantitative assessment. Preliminary findings will describe implementation outcomes and early effects on HIV care engagement.

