#### Stepped-Wedge Analysis

We will analyze intervention effects using intention-to-treat principles and generalized linear mixed models appropriate to each outcome. Models will include a fixed effect for time period (step) to account for secular trends, a fixed indicator for intervention exposure during each step (within-cluster), and random intercepts for clusters (facilities) to account for within-cluster correlation. Where appropriate, we will include random slopes for time if supported by the data. Covariates prespecified for adjustment include patient-level baseline characteristics (age, gender, income, education, and stigma) and facility-level covariates (facility size and urban or rural). We will use robust SEs (cluster-robust SEs) to ensure valid inference with a limited number of clusters. Additional sensitivity analyses will include per-protocol analyses and models testing for time-by-intervention interaction to explore whether effect sizes change across steps. Primary inference will be 2-sided with *α*=.05. Analyses will be performed in Stata (StataCorp LLC; xtmelogit/xtmixed), and code will be archived with the study repository for reproducibility.

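### The stated power of at least 80% for odds ratios of 1.7 to 2.0 in the adoption analysis does not follow from the protocol's own inputs: for a binary predictor, an odds ratio of 1.7 has at most about 53% to 60% power

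*Protocol article*

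**What the plan says.** The section Power Calculation for the Pre- and Postassessment sets out its inputs as follows.

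- Sample: "With 347 participants, an anticipated 10% attrition rate (effective n≈312), and a primary binary uptake outcome".
- Outcome: "Assuming an uptake rate of ~70% (adopters: n≈243; nonadopters: n≈104".
- Main claim: at that effective size the study has ">80% power (*α*=.05) to detect moderate associations", put at odds ratios of roughly 1.7 to 2.0 or higher, depending on predictor prevalence.
- Sensitivity claim: "Sensitivity analyses showed that with effective sample sizes ranging from 280 to 330 participants, the study would retain ≥80% power to detect odds ratios". The range meant is again 1.7 to 2.0, varying with how common the predictor is.

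The named predictors are health literacy, technology acceptance and masculinity. The section gives no predictor prevalence, formula or sidedness. The only statement on sidedness is in Stepped-Wedge Analysis: "Primary inference will be 2-sided".

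On recruitment, the Abstract reports: "A total of 307 men living with HIV were recruited across the 4 clinics". The main Results section repeats the figure.

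**The concern.** The section prints a power figure together with most of the inputs needed to check it, and the figure looks too favourable. With 70% uptake, an effective sample of 312 contains only about 94 nonadopters. That is a small group from which to detect an odds ratio of 1.7 for a two-level predictor.

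Adoption is the primary implementation outcome, and the role of masculine identity in uptake is one of the three stated aims. If the claim is taken at face value, a null result for masculinity, health literacy or technology acceptance will be read as good evidence against an odds ratio of 1.7. For a binary predictor, the chance of missing such an association is in fact 40% or more.

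**Working it through.** **Inputs from the protocol article.** Overall uptake 0.70; alpha .05; effective n of 280, 312 and 330; odds ratios 1.7 and 2.0; 347 enrolled with 10% attrition; 307 recruited.

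**Assumptions.** Two-sided test. Binary predictor with prevalence q, because the section makes the result depend on predictor prevalence. The value of q is not given, so it was scanned from 5% to 95%.

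**Method.** Let p0 and p1 be uptake without and with the predictor. They are solved from

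- (1 − q)·p0 + q·p1 = 0.70
- [p1/(1 − p1)] / [p0/(1 − p0)] = OR

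Power = Φ{ [(p1 − p0) − 1.96·s0] / s1 }, where

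- s0 = √[0.70 × 0.30 × (1/n0 + 1/n1)]
- s1 = √[p0(1 − p0)/n0 + p1(1 − p1)/n1]
- n0 = n(1 − q), n1 = nq

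**Worked case at n = 312, q = 0.5 (156 men per group).**

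- OR 1.7: p0 = 0.6448, p1 = 0.7552, difference 0.1105, s0 = 0.0519, s1 = 0.0515. The argument is (0.1105 − 0.1017)/0.0515 = 0.17, so power is 57%.
- OR 2.0: p0 = 0.6283, p1 = 0.7717, difference 0.1434, s0 = 0.0519, s1 = 0.0512. The argument is (0.1434 − 0.1017)/0.0512 = 0.81, so power is 79%.

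**Power across the stated range.**

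| OR | Prevalence | n = 280 | n = 312 | n = 330 |
|---|---|---|---|---|
| 1.7 | best (about 55%) | 53% | 57% | 60% |
| 1.7 | 50% | 52% | 57% | 59% |
| 1.7 | 30% | 42% | 46% | 48% |
| 1.7 | 20% | 31% | 35% | 36% |
| 2.0 | best (about 55%) | 75% | 79.6% | 82% |
| 2.0 | 50% | 75% | 79% | 81% |
| 2.0 | 30% | 63% | 68% | 70% |

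At the best prevalence, 80% power needs about 535 men for OR 1.7 and about 316 for OR 2.0. At 30% prevalence the numbers are 681 and 411.

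**Attempts to recover the stated figure for OR 1.7 with a binary predictor.**

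| Variant | Power, OR 1.7 |
|---|---|
| Wald test on the log odds ratio, n = 280-330 | 52-59% |
| Simulated likelihood-ratio test, n = 280-330 | 53-60% |
| One-sided test, n = 280-330 | 65-71% |
| All 347 men, no attrition | 62% |
| 70% taken as uptake in the exposed group, n = 280-330 | 56-63% |
| Uptake 50%, n = 280-330 | 60-67% |
| Adopters and nonadopters as fixed groups, 243/104 | 62% |
| Adopters and nonadopters as fixed groups, 218/94 | 57% |

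None reaches 80%.

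**Continuous predictor.** By the Hsieh formula, the odds ratio per SD detectable with 80% power is exp{(1.960 + 0.842)/√(n × 0.70 × 0.30)}. This gives 1.44 at n = 280, 1.41 at n = 312 and 1.40 at n = 330. An odds ratio of 1.7 per SD would have 98-99% power. So 1.7-2.0 is not the threshold under this coding either, and prevalence would play no part in it.

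**Adopter split.** 347 × 0.70 = 243 and 347 × 0.30 = 104, which are the printed figures. On the effective sample, 312 × 0.70 = 218 and 312 × 0.30 = 94.

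**Men recruited.** 307 lies inside 280-330. With the protocol's 10% attrition, 307 × 0.9 = 276. Odds ratios detectable with 80% power:

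| Coding | n = 276 | n = 307 |
|---|---|---|
| Binary, 50% prevalence | 2.1 | 2.0 |
| Binary, 30% prevalence | 2.4 | 2.25 |
| Binary, 20% prevalence | 2.8 | 2.6 |
| Continuous, per SD | 1.44 | 1.42 |

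**The case against.** The strongest reply is that the three predictors come from survey modules and are probably scale scores. Analysed as continuous, they give ample power: an odds ratio of about 1.4 per SD is detectable. This stands as a limit on the harm, since the study may be better powered than the binary figures suggest. It does not rescue the text, which ties its odds ratios to predictor prevalence and quotes a threshold that the continuous formula does not produce.

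A second reply is that 1.7 and 2.0 may be meant as the detectable odds ratios at the best and the least favourable prevalence. That fails too. At the best prevalence the detectable odds ratio is about 2.09 at 280 men and 1.97 at 330, and it rises as the predictor becomes less balanced.

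Three stronger readings are tempting, and the document does not support them.

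- *That the 307 men recruited fall below the sensitivity range.* They do not. Only 307 less 10% attrition, about 276, falls below it, by 4 men, and power there is within a percentage point of that at 280. Adoption is also defined within 60 days of introduction, with installation dates taken from facility data, so loss at the 8-month visit may not fully reduce this analysis. Nor is it certain that 307 is final: the Abstract says recruitment concluded in November 2025, while the main Results section expects baseline collection to run to the end of January 2026.
- *That 70% uptake contradicts the protocol's own account of the pilots.* The Introduction says of Nishauri that "its uptake and use remain low and highly variable across facilities, providers, and patient populations", but gives no percentage. It describes pilots across patient populations, whereas the 70% is for consenting smartphone or tablet owners who are trained on the app. A lower-uptake scenario would be prudent, but no error is shown.
- *That the study is underpowered for its main clinical question.* Missed appointments in the stepped-wedge component have a separate calculation, which this point does not touch.

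**Conclusion.** The concern holds for the printed power claim. For a binary predictor, the claim of at least 80% power at an odds ratio of 1.7 fails at every sample size and prevalence examined, with a best case of about 53-60%. At an odds ratio of 2.0 it holds only from about 316 men with a near-balanced predictor, and at the planned effective size of 312 it just misses (79.6%). The adopter split is a smaller slip of denominator.

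The percentages rest on 70% overall uptake, a two-sided alpha of .05 (not stated in that section) and a single binary predictor. A one-sided test raises the best case for 1.7 to only 65-71%. Whether the eventual analysis is underpowered depends on predictor coding, which the section does not state.

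This should be fixed. It affects how null associations are read, but not the primary clinical outcome or the conduct of the study.

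**What to change.** In Power Calculation for the Pre- and Postassessment:

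1. Delete the odds ratio of 1.7 and the sentence on effective sizes of 280 to 330.
2. State the predictor coding, sidedness and formula.
3. If the predictors are binary, give the odds ratio detectable with 80% power for 276-307 men by prevalence: about 2.0-2.1 at 50%, 2.25-2.4 at 30% and 2.6-2.8 at 20%. If they are continuous scores, give the odds ratio per SD instead, about 1.42-1.44. The two sets are alternatives and should not be mixed.
4. Put the adopter split on the same base as the effective sample (about 218/94 for 312), or say that 243/104 refers to all 347 enrolled.
5. Optionally, add a lower-uptake scenario, labelled as an assumption.

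The cost is a change of wording and a less favourable stated figure. No extra recruitment or data collection is needed.
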